### Recruitment and allocation

Eligible practices (see eligibility criteria above) will be identified through the Health Research Board Primary Care Clinical Trials Network, Ireland (http://primarycaretrials.ie/) and invited to participate by formal letter, including letter of agreement to participate and study information leaflets detailing the steps of the intervention. Practices will identify patients aged 65 years and over who are currently prescribed 15 or more repeat medicines using the patient finder tool, which will be integrated into practice management software in participating practices. The research team will assist practices in recruiting eligible patients, who will be sent invitation letters (on practice headed paper) with consent forms, information leaflets and questionnaires. Based on recent analysis of prescribing trends in Ireland, we anticipate that most included practices will have at least 15 eligible patients [7]. In larger practices with more than 40 eligible patients, we will randomly select 40 patients to invite, based on the OPTI-SCRIPT response rate [28]. Control practices will receive €30 per recruited patient and intervention practices €60 per recruited patient to reflect some of the costs involved in taking part in the study.

Baseline data collection will occur prior to practice allocation by review of patient prescriptions and questionnaires (see outcomes and methods for data collection below). Recruited practices will be randomly allocated, using minimisation and randomisation software, by an independent third party (Fig. 2). Minimisation will ensure balance between the groups [39, 40] in terms of practice size (number of whole-time-equivalent GPs) and location (urban versus rural). An “urban” practice is defined as being located in an area with a population of at least 5000 people, has most of its patients within a relatively small geographical area and have ready access some hospital facilities [42]. Considering the nature of the intervention, it is not possible to blind GPs or participants to the intervention.

**Fig. 2 Fig2:**
[figure not shown]
Flow of practices and patients through RCT

### The intervention

The content of the SPPiRE intervention was developed based on the OPTI-SCRIPT trial, emerging evidence and results from the SPPiRE pilot and contains the following elements:Training videos which demonstrate how to perform a SPPiRE medication review and describe the underlying evidence on polypharmacy, common potentially inappropriate prescriptions in older people, multimorbidity and treatment burden. The videos also provide guidance on establishing treatment burden and supporting patients to express their priorities, based on recommendations in the NICE multimorbidity guideline [6].An online medication review template (see Fig. 3) which provides a structured process and links to alternative strategies for each identified PIP. The GP will be guided to:Screen the prescription for PIP, including the requirement for monitoring and if duplicate drug classes are present.Assess the patient’s treatment priorities and consider whether on-going symptoms may represent adverse drug reactions.Review each medicine with the patient assessing the effectiveness of symptomatic treatment, the relative harms and benefits of preventative treatment, the presence of adverse drug reactions and whether each medicine is being taken as prescribed.Agree all changes with the patient, taking into account their treatment priorities and considering suggested treatment alternatives for identified PIP.Print out a summary document which will be generated upon completion of the review. This will outline all changes and any action that needs to be taken, including the need for blood monitoring if indicated.

**Fig. 3 Fig3:**
[figure not shown]
SPPiRE medication review process. Abbreviations: *PIP* potentially inappropriate prescription, *ADR* adverse drug reaction

Any medication changes will be at the discretion of the prescribing GP, weighing up the risks and benefits and incorporating patient preference.

The control arm will continue to deliver usual care for the 6-month study duration. Usual care will vary from practice to practice, and differences in repeat prescribing policies between clusters will be identified and described using a baseline practice profile questionnaire. Following 6-month data collection and completion of the RCT, control arm GPs will be invited to participate in the intervention as outlined above. No further RCT data will be collected from participants on trial completion at 6 months. However, we will ask intervention practices to submit prescription data at 12 months to examine whether changes in prescriptions have been maintained.

### Contemporaneous national control–PCRS dataset

We will also analyse national prescription patterns via the Health Service Executive (HSE) primary care reimbursement service (PCRS) prescription database. This is a national prescribing database based on GP and pharmacy claims in a number of community schemes, including the General Medical Services (GMS) scheme. In 2014, 70% of people aged over 65 years in Ireland were covered by the GMS scheme and so their prescription data are captured in the PCRS database [43]. Anonymised data from the PCRS GMS database can be used to provide a contemporary national control. Comparisons to previous national prescribing patterns for those aged 65 years and over being prescribed 15 or more medicines will determine if there has been a change over time at the population level [7].

### Outcomes measures

Outcome measures pertain to the individual patient level and have been specifically chosen to reflect the potential effects of the intervention and to incorporate the patient perspective. Baseline data will be collected prior to allocation using the PMS, patient questionnaires and a practice profile questionnaire. Follow-up data will be collected 6 months following completion of each medication review in intervention patients through review of the PMS and patient questionnaires and 6 months following the median date of all the medication review dates in control practices.

*Primary outcomes:*
Proportion of patients with any PIP (see Tables 2, 3, and 4)Mean number of repeat medications, defined as any medicine with an ATC code for which the patient is currently in receipt of a repeat prescription.

*Secondary outcomes:*
Reduction in proportion of patients with 15 or more medicines (100% at baseline)Medication changes○ Number of medications stopped (per patient and absolute number in intervention versus control)○ Numbers of medications started (per patient and absolute number in intervention versus control)○ Reduction in the number of PIP (per patient and absolute number in intervention versus control)○ Proportion of patients with any reduction in PIP
Multimorbidity Treatment Burden Questionnaire (MTBQ) [44]Health related quality of life (EQ5D-5L) [45]Revised Patients’ Attitudes Towards Deprescribing (rPATD) [46]Health service utilisation per patient (based on chart data and collected on both time periods (baseline and 6 months post-intervention completion), at study completion by the research team○ Number of GP/practice nurse visits○ Number of out-of-hours visits○ Number of Accident & Emergency (A&E) visits○ Number of emergency hospital admissions and reason for admission○ Number of in-patient days○ Number of out-patient visits
Patient-reported adverse drug withdrawal events (ADWEs) from follow-up patient questionnaire (defined as either recurrence of the condition for which the drug was prescribed or a physiologic reaction to drug withdrawal.) [47, 48]

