### Sample size

Sample size for the primary outcome (proportion with PIP) is based on a prevalence of approximately 40% for PIP in this population [7]. To reduce this to 20% requires a sample size of 240 patients. The sample size also needs to be adjusted to reflect the assumption that individual outcomes are not independent of each other, as participants in the same cluster may respond in the same way. Hence, an intra-cluster correlation coefficient (ICC) of 0.025 will be used. This was also used in the OPTI-SCRIPT study and was based on an observational study of an elderly cohort in the HRB Centre for Primary Care Research [49]. This gives a design effect size of 1.35, thus inflating the sample to 324 patients from 22 practices. An equal cluster size of 15 patients per practice has been assumed.

All the patients in this study will be selected on the basis of receiving 15 or more repeat medicines on their prescription. Existing data from the Irish national prescribing database (HSE-PCRS) highlights that in those aged 65 years and over on 15 or more repeat medicines, the mean number of medicines is 17.4 (SD 2.69) [7]. A meta-analysis of deprescribing trials reported a difference between treatment groups of 0.4 medicines where the mean number of medicines was 7.4 [50]. We are targeting patients on at least 15 repeat medicines and for primary outcome, number of repeat medications, will test for a mean difference of one medicine between the intervention and control group and this would require a sample size of 306 patients. This is inflated by the design effect size outlined above (1.35) to give a sample of 413 patients from 28 practices.

Factoring in a loss to follow-up of approximately 10% (for primary outcomes, based on chart data) and using the higher numbers required to demonstrate a significant reduction in mean number of repeat medicines, a total of 30 GP practices and 450 patients will be required.

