### Monitoring and participant safety

A Trial Steering Committee (TSC) comprising an independent chair and two other independent members, one of whom is a lay member representing the patient and public perspective, has been established and will oversee the progress of the trial and adherence to the study protocol. It was agreed by the TSC that given the low risk nature of the trial, lack of interim data and relatively short term follow-up, that there is no need for the establishment of a Data Monitoring Committee.

A formal process has been developed to capture any potential adverse events related to discontinuing medication. Recruited practices will be instructed in the practice recruitment leaflet on how to report any suspected adverse effects from deprescribing. Any adverse events will also be captured by a chart review at follow-up data collection. An assessment on likely causality will then be made using an adapted drug withdrawal probability scale [48]. Patient-reported ADWEs will also be collected as a secondary outcome measures in the follow-up patient questionnaire, 6 months after intervention completion. Any patient safety concerns arising during the course of the trial, including at baseline data collection, will be brought to the attention of the Trial Steering Committee.

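### The one outcome defined as a harm rests on unblinded patient report at 6 months; the chart-identified, causality-rated withdrawal events already planned should be listed beside it

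*Protocol article*

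**What the plan says.** The secondary outcomes in the Protocol article, Outcomes measures, include "Patient-reported adverse drug withdrawal events (ADWEs) from follow-up patient questionnaire". An adverse drug withdrawal event (ADWE) is "defined as either recurrence of the condition for which the drug was prescribed or a physiologic reaction to drug withdrawal". The section Monitoring and participant safety repeats both source and status: "Patient-reported ADWEs will also be collected as a secondary outcome measures in the follow-up patient questionnaire, 6 months after intervention completion".

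That same section describes a second route. Practices are told how to report suspected harm from deprescribing, and "Any adverse events will also be captured by a chart review at follow-up data collection". It goes on: "An assessment on likely causality will then be made using an adapted drug withdrawal probability scale". Events found this way do not appear in the outcome list.

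Follow-up is scheduled in both arms. For the intervention arm, "Follow-up data will be collected 6 months following completion of each medication review in intervention patients through review of the PMS and patient questionnaires"; for the control arm, the time is "6 months following the median date of all the medication review dates in control practices".

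The outcome list also has chart-based health service use, including out-of-hours and emergency department visits, emergency admissions with their reason, and in-patient days. The Discussion accepts that patients, GPs and study staff cannot be blinded, and offers the objectivity of the primary outcomes as partial mitigation.

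**The concern.** The intervention works partly by stopping medicines, and the stated aim includes safer prescribing. Readers will therefore look for a comparison of withdrawal harm between arms. As defined, an ADWE is a causal judgement: it needs to be known which drug was stopped, when, for what indication, and what followed. The listed outcome leaves that judgement to the patient, months later and with allocation known. The mitigation offered in the Discussion concerns the primary outcomes and does not reach this one.

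Patients who die, or who are too ill to return the form, contribute no patient-reported ADWE. The chart route does not depend on the form being returned, and it applies a structured causality assessment. Because it is not a listed outcome, the article fixes no comparison of its results between arms.

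**Working it through.** **Step 1. The two routes side by side.**

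| | Patient-reported ADWEs | Chart-captured events |
|---|---|---|
| Where described | Outcomes measures; Monitoring and participant safety | Monitoring and participant safety only |
| Listed secondary outcome | Yes | No |
| Who identifies the event | Patient, allocation known | Chart reviewer, allocation known |
| Depends on questionnaire return | Yes | No |
| Causality scale described | No | Yes |

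The two sections do not contradict each other. The gap is that the second route leads to no listed comparison.

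**Step 2. Do the utilisation outcomes fill the gap?** Only in part. Emergency visits and admissions do not depend on the questionnaire and can show serious harm. They are counts of service use, though, and the plan does not link them to a stopped drug. A withdrawal reaction or recurrence managed without an emergency contact would not appear in them.

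**Step 3. What can be quantified.** The article gives no ADWE risk, questionnaire response rate or detection fraction for either source, so there is no figure to reproduce. Everything below is assumed and serves only to show direction.

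Let p be the true risk and s the fraction of events reported, with subscripts I (intervention) and C (control). The observed difference is

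D = p_I × s_I − p_C × s_C.

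With p_I = 10% and p_C = 5%, the true difference is 5.0 points.

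| s_I | s_C | Calculation | Observed difference |
|---|---|---|---|
| 100% | 100% | 10.0 − 5.0 | 5.0 points |
| 50% | 50% | 5.0 − 2.5 | 2.5 points |
| 50% | 80% | 5.0 − 4.0 | 1.0 point |
| 80% | 50% | 8.0 − 2.5 | 5.5 points |
| 100% | 50% | 10.0 − 2.5 | 7.5 points |

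Equal under-reporting shrinks the difference. Unequal reporting can shrink or enlarge it. The same formula applies to chart detection, so the chart measure is not immune if the arms are searched or documented differently.

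**Step 4. Loss of events through non-response alone.** Take 450/2 = 225 patients per arm, a 10% risk, and return unrelated to having had an event. Expected events are 225 × 0.10 = 22.5. With 90%, 70% or 50% return, the questionnaire sees 20.25, 15.75 or 11.25 of them. A chart review that reaches non-responders avoids this particular loss.

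**The case against.** The strongest reply is that the plan already covers harm from several directions. Utilisation outcomes come from charts, practices report suspected harm, and charts are reviewed for adverse events. Patient report is a deliberate choice to include the patient's perspective, and tabulating captured events by arm may belong to a full protocol or SAP that is not shown. Much of this stands: the harm assessment does not rest on the questionnaire alone, and events it misses can still reach safety oversight. What remains is that the article names the ADWE outcome and its source in two places, and leaves the causality-rated chart events out of both statements.

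A second reply is that charts are not plainly the better source. GPs and study staff know the allocation. Intervention reviews also produce a written summary of medication changes, and control patients have no such review, so stops may be better documented in one arm. This stands, and it rules out replacing the patient report with the chart measure.

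A reader might go further and infer that harm is likely undercounted. The documents do not support that. Suppose risks of 12% and 6%, with 75% of patients without an event returning the form and 50% of those with one. Responders then show 0.06/0.72 = 8.3% and 0.03/0.735 = 4.1%, so the absolute gap falls from 6.0 to 4.3 points. The odds ratio does not move: (0.12/0.88)/(0.06/0.94) = 2.14 and (0.06/0.66)/(0.03/0.705) = 2.14. If patients with an event return 90% of forms instead, the figures are 0.108/0.768 = 14.1% and 0.054/0.759 = 7.1%, and the gap grows to 6.9 points. The direction is set by the assumption. Knowing that medicines were stopped could also raise reports in the intervention arm.

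Nor is the loss allowance a defect here. The "loss to follow-up of approximately 10% (for primary outcomes, based on chart data") sizes the primary outcomes and says so; an unpowered secondary outcome needs no allowance of its own. Finally, that chart events are collected on every patient is an inference from the follow-up schedule, since the monitoring section does not say it.

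**Conclusion.** The point holds in a limited form. The only outcome defined as a harm relies on unblinded patient report at 6 months, and the planned chart-identified, causality-rated events have no listed comparison between arms. The patient-reported comparison may miss events or be biased either way. Its likely error cannot be sized from the article, and the 1.0 to 7.5 point range rests wholly on assumed risks and reporting fractions. A small ADWE difference from this source alone would be weak reassurance, and a large one would be open to the charge of reporting bias. No primary outcome or sample size figure is affected. This is a low-cost improvement to the outcome list, and it assumes that the follow-up chart review is carried out in both arms.

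**What to change.** In Outcomes measures, keep the patient-reported ADWEs and add beside them: the proportion of patients with at least one chart-identified ADWE, rated on the adapted withdrawal probability scale. Compare it between arms over all randomised patients with chart follow-up, including those who died or did not return a questionnaire.

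State that the chart-review procedure and the length of the look-back window are the same in both arms. The window needs a defined start in each arm, because follow-up is timed from each patient's own review in the intervention arm and from the median review date in the control arm. Say in Monitoring and participant safety that the review covers all patients in both arms, if that is the intention.

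Any rate per medicine stopped should be descriptive only. The number of stops arises after randomisation and the intervention is meant to change it, so a comparison on that denominator is no longer a randomised one.

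**Cost.** Collection and scoring are already planned, so the additions are outcome wording and a common review procedure, with some effort to apply it evenly. Charts may miss mild events, and both the review and the scoring remain unblinded. The two measures should therefore be reported together.

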### Plan of analysis

Descriptive statistics (proportions, means) will be used to evaluate differences in baseline characteristics between participating GP practices and patients in the two arms of the trial. The primary analysis will be carried out using multilevel modelling. The primary outcome measure, proportion of patients with or without a PIP, will be a binary outcome measure and will be compared between treatment arms using random effects logistic regression with individuals as the unit of analysis and the practice included as the random effect.

The second primary outcome measure, number of repeat medications, will be assessed using a random effect Poisson regression with the individual as the unit of analysis and the practice included as the random effect to control for the effects of clustering. Incidence rate ratios (IRR) and 95% confidence intervals (CI) will be presented. All analysis will be conducted under the intention-to-treat principle as this is a pragmatic trial [39].

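### As written, both primary models omit the patient's baseline value and the two minimisation factors: the comparison stays valid but gives up precision that is cheap to recover

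*Protocol article*

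**What the plan says.** Plan of analysis describes each primary model by its class, its unit of analysis and its random effect. It has any-PIP status "compared between treatment arms using random effects logistic regression with individuals as the unit of analysis and the practice included as the random effect". For the number of repeat medicines it names a "random effect Poisson regression with the individual as the unit of analysis and the practice included as the random effect", reported as an incidence rate ratio. No fixed effect other than arm is mentioned or implied for either. The only use the section gives for baseline data is descriptive: summary statistics "will be used to evaluate differences in baseline characteristics between participating GP practices and patients in the two arms of the trial".

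Two other sections show what is available:

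- Recruitment and allocation: "Baseline data collection will occur prior to practice allocation by review of patient prescriptions and questionnaires". Practices are then minimised on number of whole-time-equivalent GPs and on urban or rural location.
- Outcomes measures: baseline data also come from the practice software before allocation. One secondary outcome is the per-patient reduction in number of PIPs, so a baseline PIP count has to be derived in any case.

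The Sample size section has no covariate term for either outcome.

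**The concern.** A patient's medicine count or PIP status at baseline is likely to be among the best available predictors of the same measure six months later. The outcome counts repeat items, which tend to persist. In the ten-patient pilot the mean count moved only from 17.5 to 16.8 immediately after review, and 44% of identified PIPs were acted on, so 56% were not. That is indirect evidence, but it points towards a useful correlation.

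If these predictors are left out of the model, two things follow. The variation that patients bring with them from baseline stays in the residual, so the intervals are wider than they need be. And with only 30 randomised units, a chance difference between arms in baseline count or PIP passes into the point estimate without correction. Leaving out the minimisation factors also means that the model-based standard error takes no account of the balance that minimisation produced, which errs on the conservative side.

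**Working it through.** **1. Reproduce the plan's figures.** The article does not state alpha or power. Two-sided 0.05 and 90% power are assumed because they recover its numbers.

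- Count: n per arm = 2(1.960 + 1.282)² × 2.69² / 1² = 152.07, rounded up to 153, so 306 in total, as stated.
- PIP, 40% to 20%: 238 with continuity correction, against the stated 240.
- Design effect: 1 + 14 × 0.025 = 1.35. Then 306 × 1.35 = 413 and 240 × 1.35 = 324, as stated.
- Dropout: 413 / 0.9 = 459, against the planned 450 (2% apart). Patients analysed: 450 × 0.9 = 405.

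All of this works without a covariate, so the sample size does not rely on adjustment.

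**2. Count outcome on a linear scale.** The effective number per arm is 405 / 1.35 / 2 = 150. Adjustment for a baseline value with correlation r reduces the SD to 2.69√(1 − r²). Then SE = SD × √(2/150) and power = Φ(1/SE − 1.96). The design effect is held at 1.35. The values of r are assumptions.

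| r | Residual SD | SE | Power for 1 medicine | Difference detectable at 90% power | Analysed N for 90% power |
|---|---|---|---|---|---|
| unadjusted | 2.69 | 0.311 | 89.6% | 1.01 | 414 |
| 0.3 | 2.57 | 0.296 | 92.1% | 0.96 | 376 |
| 0.5 | 2.33 | 0.269 | 96.1% | 0.87 | 311 |
| 0.7 | 1.92 | 0.222 | 99.5% | 0.72 | 211 |

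**3. If the follow-up SD exceeds 2.69.** That figure describes people selected for having 15 or more medicines. Follow-up counts can fall below 15, and the pilot SD went from 3.41 to 3.94 (ten patients). With the same formula:

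| Follow-up SD | Unadjusted | r = 0.5 | r = 0.7 |
|---|---|---|---|
| 2.69 | 90% | 96% | 99% |
| 3.11 (= 2.69 × 3.94/3.41) | 80% | 90% | 97% |
| 3.94 | 59% | 72% | 87% |

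**4. The named Poisson model.** It fixes the variance at the mean, 17.4 (SD 4.17). The article's SD gives 2.69² = 7.24, a ratio of 7.24/17.4 = 0.42. In simulation (28 practices of 15, r = 0.5 and 0.7) the standard error of the log rate ratio was 0.0238 with and without the baseline count. Power moved only from 72–77% to 75–79%, and type I error was about 1% unadjusted and 0.2–0.5% adjusted. These fits omitted the practice random effect, whose variance would be estimated near zero for counts this underdispersed. Linear fits to the same data did gain: at r = 0.7 the standard error fell from 0.297 to 0.239.

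**5. PIP outcome.** An illustrative logistic simulation used effective N 300, 40% prevalence at baseline and in controls, and a conditional log odds ratio fixed at −0.75. Adjustment for baseline PIP raised power from 82% to 84%, 67% to 77% and 32% to 55% at baseline-to-follow-up correlations of 0.25, 0.5 and 0.75. These do not describe the design effect size: for 40% to 20%, unadjusted power with 405 analysed is 96.9%.

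**6. Minimisation factors.** At ICC 0.025, practice-level factors can account for at most 2.5% of outcome variance. If the two factors explained 10% to 20% of the between-practice part (an assumption), the design effect would fall from 1.35 to 1 + 14 × 0.0225 = 1.315 or 1 + 14 × 0.02 = 1.28. The standard error would fall by 1 − √(1.315/1.35) = 1.3% or 1 − √(1.28/1.35) = 2.6%.

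**The case against.** The strongest reply is that this is silence, not a decision. The article is condensed, its SAP is not shown, and a covariate list is a usual SAP item. Plan of analysis nowhere calls the models unadjusted. A reader might infer that the investigators have ruled out covariates; the text does not support that. What remains is that the section specifies the primary analysis down to the random effect and effect measure, gives baseline data a descriptive role only, and sits beside a sample size with no covariate term. Read as written, the models are unadjusted.

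Second, a reader might infer bias or an invalid test. Neither follows. Baseline data precede allocation, the randomised comparison is valid without adjustment, and the confidence interval already allows for chance imbalance. This objection stands in full.

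Third, a reader might infer that the trial is badly underpowered without adjustment. Simulations that add a change with SD 2 to 3 to the baseline count do give unadjusted power between 57% and 81%, and 73% to 99% adjusted. But they assume a follow-up SD of about 3.35 to 4.0, while the article plans on 2.69, where unadjusted power is 89.6%. Much of that apparent shortfall comes from the assumed SD, so those figures are not properties of this trial.

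Fourth, all ten pilot patients had at least one PIP, and 90% did without the proton pump inhibitor criterion, whereas the sample size "is based on a prevalence of approximately 40% for PIP in this population". If baseline prevalence resembles the pilot, a yes/no baseline covariate is nearly constant and adds little. This stands, and it is why the number of PIPs is the better covariate. The pilot's 44% also records action at the review, not persistence at six months.

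**Conclusion.** The point holds as one of lost efficiency. Both primary models, as written, omit the baseline value of the outcome and the two minimisation factors, although all will be known before allocation. For the count, the benefit at the article's own SD runs from about 2 to 10 percentage points of power over r = 0.3 to 0.7, or a 9% to 49% cut in residual variance (r²). It is larger if the follow-up SD exceeds 2.69. The direction is firm, but the size rests on a correlation and a follow-up SD that the article does not give. Entry at 15 or more medicines truncates the baseline count and may lower r. The power figures use normal quantiles, so they run slightly high for 30 clusters in both columns. The count gain is realised only if the model estimates its variance. The contribution of the minimisation factors is probably small. Amending the plan is worthwhile, but validity does not depend on it.

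**What to change.** State in Plan of analysis, before outcome data are seen, that the primary analysis of each outcome includes as fixed effects:

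- the patient's baseline value: medicine count for the count outcome, and number of PIPs in preference to yes/no for the PIP outcome;
- practice size (whole-time-equivalent GPs) and urban or rural location.

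For the count, use a model that estimates the variance: a linear mixed model, or Poisson with robust or scaled standard errors if the incidence rate ratio is to be kept. Apply a small-sample correction for about 30 clusters, since uncorrected cluster-robust linear fits in the simulations above rejected a true null 6% to 8% of the time. For PIP, report a marginal risk difference beside the odds ratio. Keep the unadjusted models as sensitivity analyses. If the SAP already says this, one cross-reference in the article's text is enough.

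The cost is low. No new data are needed and the sample size is unchanged. The adjusted odds ratio becomes conditional on the covariates, which has to be explained to readers, a linear model would replace the rate ratio by a mean difference, and the analysis takes slightly more work. Fixing the choice now also prevents a decision to adjust from being prompted later by the descriptive comparison of the arms at baseline.

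### The Poisson model for number of repeat medicines cannot reproduce the variance the trial was sized on; if the 6-month SD is near 2.69, standard errors are about a third too large and power falls from about 90% to about 74%

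*Protocol article*

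**What the plan says.** Protocol article, Plan of analysis, on the second primary outcome: "number of repeat medications, will be assessed using a random effect Poisson regression with the individual as the unit of analysis". Practice is the random effect, included to handle clustering. On reporting: "Incidence rate ratios (IRR) and 95% confidence intervals (CI) will be presented". The section mentions no dispersion parameter, quasi-likelihood or robust standard error.

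Protocol article, Sample size, on the same outcome: "the mean number of medicines is 17.4 (SD 2.69"), a figure for national-database patients aged 65 and over who are on 15 or more medicines. The target is a mean difference: "will test for a mean difference of one medicine between the intervention and control group and this would require a sample size of 306 patients". Clustering enters through two statements, "an intra-cluster correlation coefficient (ICC) of 0.025 will be used" and "An equal cluster size of 15 patients per practice has been assumed", and then: "This is inflated by the design effect size outlined above (1.35) to give a sample of 413 patients from 28 practices". This outcome needs more patients than the other primary outcome, so it sets the final 450 patients and 30 practices.

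**The concern.** A Poisson model ties each patient's variance, given the practice effect, to the mean. A practice random effect can only add to that, so the marginal variance in the model is at least the mean, about 17. The sample size rests on a variance of 7.24, which is low because everyone in the planning population was selected at 15 or more medicines. No value of the random effect brings the model down to that variance.

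If the follow-up data resemble the planning data, the confidence interval will be too wide and the test too cautious. The outcome that determines the size of the trial would then be analysed with less power than the sample size was meant to buy. The clustering term would also do nothing, because the excess Poisson variance already covers the variation between practices.

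**Working it through.** **Inputs.** From Sample size: mean 17.4, SD 2.69, difference 1, ICC 0.025, 15 patients per practice, 306 and 413 patients. From the pilot Results: SD 3.41 before review and 3.94 after, in 10 patients. Assumed, because not stated: two-sided alpha 0.05, 90% power, equal arms.

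**1. The plan's own figure.** Per arm, n = 2 × (1.960 + 1.282)² × 2.69² / 1² = 152.1, rounded up to 153, so 306 in total. This matches exactly; 80% power would give 228, and one-sided 90% would give 248. Design effect: 1 + 14 × 0.025 = 1.35. Then 306 × 1.35 = 413, and 413/15 = 27.5, so 28 practices. The sizing is therefore a normal two-means calculation with variance 2.69² = 7.24.

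**2. Standard errors at 413 patients (206.5 per arm), SD 2.69.**
- Correct, with clustering: √(2 × 7.24 × 1.35 / 206.5) = 0.308.
- Poisson, practice variance at zero: √(2 × 17.4 / 206.5) = 0.411 (0.4105 before rounding).
- Ratio: √(17.4 / (7.24 × 1.35)) = 1.33.

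**3. Why the practice variance goes to zero.** Poisson noise in a practice mean is 17.4/15 = 1.16. The whole planned variance of a practice mean, clustering included, is 7.24 × 1.35 / 15 = 0.65. The model sees less between-practice variation than it expects from chance alone.

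**4. Consequences at SD 2.69.**
- Power with the correct SE: Φ(1/0.308 − 1.96) = 90%.
- Power with the Poisson SE: Φ((1 − 1.96 × 0.4105)/0.3076) = Φ(0.635) = 74%. With the arms averaged at 16.9 it is 75%; with the 405 patients left after 10% loss from 450 it is 73%.
- Type I error: 2 × (1 − Φ(1.96 × 1.335)) = 0.9%.
- Sizing on a variance of 17.4 at 90% power would need 732 patients, or 988 after the design effect.

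**5. Simulation check.** 28 practices of 15 patients, SD 2.69, ICC 0.025, random-intercept Poisson fitted by quadrature, 1,500 trials per scenario. The Poisson model rejected in 75% of trials with a one-medicine difference and in 0.9% under the null. A cluster-level t-test on the same data gave 89% and 4.6%. The estimated practice SD on the log scale was below 0.02 in over 99% of trials.

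**6. Sensitivity to the 6-month SD.** Same formulas, 413 patients, mean 17.4, Poisson SE 0.4105 with practice variance at zero:

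| SD | Variance | Correct SE | SE ratio | Power, correct SE | Power, Poisson SE |
|---|---|---|---|---|---|
| 2.69 | 7.24 | 0.308 | 1.33 | 90% | 74% |
| 3.41 | 11.63 | 0.390 | 1.05 | 73% | 69% |
| 3.94 | 15.52 | 0.451 | 0.91 | 60% | see below |

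The ratio reaches 1 at SD = √(17.4/1.35) = 3.59. At SD 3.94 the expected variance of a practice mean is 15.52 × 1.35 / 15 = 1.40, above 1.16. The practice variance can then be estimated as positive, which would raise the Poisson SE, so no Poisson power is given for that row.

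**The case against.** The strongest objection is that 2.69 is not the SD of the outcome. It describes a cross-section cut off at 15 medicines. The outcome is the 6-month count, when that floor no longer applies; the article itself lists the proportion still at 15 or more as a secondary outcome. No 6-month SD is given, and the pilot SDs, weak as they are at 10 patients, are both larger. This stands. A reader might infer that standard errors will be a third too large whatever the data, and that the clustering adjustment must vanish. The documents support neither without the condition that the SD is near 2.69. At SD 3.94 the excess is gone, and the more pressing trouble is that 413 was computed from too small an SD.

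Second, the error is conservative at the planning SD: it costs power and does not create false positives. This also stands and limits the severity.

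Third, a reader might infer that the incidence rate ratio is itself a mistake. It is not: one medicine off 17.4 is a ratio of 16.4/17.4 = 0.943, and a test of that ratio has the same null. Nor can the plan be faulted for how Poisson would handle a baseline covariate, since it names none for this model and gives no correlation with baseline.

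Fourth, robust standard errors could be specified in an analysis plan that is not shown. That would settle the matter in substance. But the article does not leave the model open: it names one whose variance assumption conflicts with its own sample size. That is a choice fixed badly, not a detail left out.

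**Conclusion.** The concern holds, conditionally. On the plan's own figures (mean 17.4, SD 2.69, ICC 0.025, 413 patients) the stated model gives a standard error about 1.33 times the correct one, type I error of about 1%, and power of about 74-75% for a one-medicine difference, against about 90%. Put plainly, a true one-medicine effect would be missed about one time in four instead of one in ten. The 90% is inferred from the exact match to 306.

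The size depends on a 6-month SD that the article does not give. The loss is small at 3.41 and absent at about 3.6 and above, where the planning SD is itself too low. Power is reduced, not abolished, and the error is on the cautious side. This should be fixed, but it does not threaten the validity of a positive result at the planning SD.

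**What to change.** Preferred: make the primary analysis of this outcome a linear mixed model with a practice random intercept and small-sample degrees of freedom for about 30 practices. Report the mean difference in medicines with its 95% confidence interval. This matches the outcome as defined under Outcomes measures and the quantity used in Sample size.

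Alternative, if the incidence rate ratio is kept: use practice-level robust standard errors with a small-sample correction, or an estimated dispersion parameter that may fall below one, so that the standard error follows the observed variance. If the analysis plan already does this, say so in the protocol.

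Either change costs one sentence, made before any comparison of the arms, and needs no further data. Neither restores power if the 6-month SD proves well above 2.69. State alpha and power for the calculation at the same time, and acknowledge that the planning SD comes from a population selected at 15 or more medicines.
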